### Sample Size

To estimate the sample size, we used the open-source R Shiny application for cluster randomized controlled trials with a parallel design and discrete time decay correlation structures for multiple periods [36] available at [37]. Further, we assumed *t*-distribution due to plans for small sample corrections at the analysis stage in accordance with the report by Rutterford et al [38]. The study was approved for 4 years, but the core research team foresaw it feasible to actively collect data for a period of 3 years considering university semester breaks, public holidays, and unexpected events, such as COVID-19–related interruptions, which led to suspension of the trial for 12 months from March 2020 to March 2021. The 3 years (36 months) would yield 12 study periods given the planned training of cohorts of medical students on a 3-monthly basis in accordance with the average duration of internship deployment by the Ugandan Ministry of Health (1-5 months) and the average duration of surgery clinical rotation for university medical students (2 months).

Fixing the study power at 80% for a parallel cluster randomized trial with different cross-sections, considering a discrete time decay period of every 3 months for a total of 12 periods, and assuming correlations to decay with each period, we explored the minimum number of patient participants (cluster size) required per period using the R Shiny application [36]. Assuming a significance level of .05, a within-period intraclass correlation coefficient (ICC) of 0.02 (lower extreme: 0.01, upper extreme: 0.05), and a cluster autocorrelation coefficient (CAC) (ratio of between-period ICC to within-period ICC) of 0.8; allowing for varying cluster sizes with a coefficient of variation of 0.5; and considering a mean difference of 1.02 hours in prehospital transfer time and a pooled standard deviation of 1.64 hours as continuous outcomes reported in a previous observational study from the United States [39], the upper ICC and base CAC plateaued between 5 and 10 participants (Figure 2).

Considering a maximum of 10 participants per cluster period, an 80% power could be attained (Figure 3) and could be met with a total of 3 clusters per arm (Figure 4). This indicates a total of 6 study centers (clusters) drawn from a pool of 17, which reasonably represents 35.3% of Uganda’s regional referral hospitals.

**Figure 2 figure2:**
[figure not shown]
Reduction in the number of clusters required with an increase in the cluster-period size at a fixed power of 0.8. CAC: cluster autocorrelation coefficient; ICC: intraclass correlation coefficient.

**Figure 3 figure3:**
[figure not shown]
Cluster-period size of 10 meeting the required power of 0.8 for 12 periods. CAC: cluster autocorrelation coefficient; ICC: intraclass correlation coefficient.

**Figure 4 figure4:**
[figure not shown]
Three clusters per arm meeting the minimum required power of 0.8 for 12 periods. CAC: cluster autocorrelation coefficient; ICC: intraclass correlation coefficient.

The sample required per arm is calculated as follows: 10 participants per cluster period multiplied by 12 cluster periods multiplied by 3 clusters, yielding a total of 360 participants. The total sample required for 2 arms would be 720. However, we inflated the sample and variance to cater to the clustering design effect based on the assumption that this increases the statistical power in accordance with the repost by Hemming et al [36]. Thus, the derived sample size (s) is calculated using the following formula:

s = n (1 + [m − 1] ρ) **(1)**

where s is the required sample size, m is the cluster size per period (ie, 10), and ρ is the within-period ICC (0.02).

This formula yields a total of 850 participants.

We will add a rate of loss to follow-up of 18% assuming the worst scenario based on our previous dropout rate of 9% in a feasibility study [7]. Therefore, the final sample will include approximately 1003 participants. Assuming an equal allocation ratio of 1:1, there will be 502 participants per arm and about 168 individuals per cluster. This sample is deemed feasible considering the high trauma burden in Uganda. According to a study at one of the Ugandan rural regional referral hospitals, a total of 900 motorcycle accident–related injuries were recorded during a 3-year period, of which 30.9% (278/900) and 15.8% (142/900) of patients sustained musculoskeletal and neurological injuries, respectively [8]. We will not compute sample sizes for each individual secondary outcome as previous studies have not reported any difference in mortality [40].

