### Study Limitations

Despite the strengths of this trial, we anticipate some limitations. First, while the authors are ambitious to assume that the study centers are homogeneous, the heterogeneity among the 6 participating regional referral hospitals could cause bias and affect study estimates. Further, the relatively smaller number of clusters could affect the power of the study. However, randomization of 6 out of the 17 trauma centers is within the ethical constraints as this sample already represents 35.3% of Uganda’s regional referral hospitals. To overcome the statistical power bias limitation, the sample size is inflated for individual randomization to cater to the design effects in accordance with the report by Hooper et al [45]. Moreover, we plan to use mixed effects regression models, which permit adjustments for covariates at both the cluster and individual levels in a single-stage approach, and plan to use the *t* test, which is robust in terms of normality deviations. According to Borhan et al [52], mixed effects models are deemed suitable for smaller clusters in situations where the primary outcomes are continuous, which is the case in this trial. Further, we hope that the ancillary studies with mixed methods will add value to the overall interpretation of the trial results by providing data from individuals outside the health sector, such as traffic law enforcement professionals.

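### The recruitment target of 1003 counts clustering twice and adds dropout by the wrong formula, and the inflation does not offset the small number of hospitals

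*Protocol article*

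**What the plan says.** The Sample Size section uses an online calculator for parallel cluster trials with several periods. The starting point is "Fixing the study power at 80% for a parallel cluster randomized trial with different cross-sections". For the correlation within a hospital and period, the plan takes "a within-period intraclass correlation coefficient (ICC) of 0.02 (lower extreme: 0.01, upper extreme: 0.05"). Between periods, the cluster autocorrelation is set at 0.8, so that correlation decays over 12 three-month periods. Cluster sizes vary with a coefficient of variation (CV) of 0.5, the difference is 1.02 hours with an SD of 1.64 hours, and a t-distribution is used. The result is "Considering a maximum of 10 participants per cluster period, an 80% power could be attained", met with 3 hospitals per arm.

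The text after Figure 4 multiplies this out to 360 per arm and 720 in total. It continues: "we inflated the sample and variance to cater to the clustering design effect based on the assumption that this increases the statistical power". The formula is n(1 + [m − 1]ρ) with m = 10 and ρ = 0.02, giving 850. An 18% loss to follow-up is then added: "Therefore, the final sample will include approximately 1003 participants".

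The Study Limitations section returns to the small number of clusters. As a way of overcoming that power limitation it says "the sample size is inflated for individual randomization to cater to the design effects".

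**The concern.** There are three faults in what the protocol states.

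- **Clustering twice.** A design-effect factor turns an individually randomised sample size into a clustered one. Here it is applied to a figure from a calculator that had already been given the ICC, the cluster autocorrelation and the CV. Study Limitations describes the step as inflating an individually randomised size, which does not fit 720.
- **Dropout.** Multiplying by 1 + d does not preserve the intended number after a proportion d is lost; dividing by 1 − d does.
- **Rationale.** The inflation is said to increase power and is offered as the answer to having only 6 hospitals. With the number of hospitals fixed, the between-hospital part of the variance does not shrink as more patients are added at each hospital.

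At stake is whether the headline sample size has a valid derivation, and whether readers are wrongly told that the few-cluster weakness has been dealt with.

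**Working it through.** **Inputs (all from Sample Size):** difference 1.02 h; SD 1.64 h; α 0.05; power 80%; ICC ρ = 0.02 (upper 0.05); cluster autocorrelation 0.8 per period; CV 0.5; T = 12 periods; m = 10 per hospital-period; 3 hospitals per arm; loss 18%, against 9% in the feasibility study. **Assumed, because not stated:** two-sided test; 4 df (6 hospitals − 2).

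**1. The plan's own figures reproduce.**
- 10 × 12 × 6 = 720.
- 720 × (1 + 9 × 0.02) = 720 × 1.18 = 849.6, rounded to 850.
- 850 × 1.18 = 1003. That both factors equal 1.18 is a coincidence: the first is the design effect, the second is 1 + 0.18.

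**2. Is 720 an individually randomised size?**
- Per arm: 2 × [1.64 × (1.96 + 0.8416) / 1.02]² = 40.6, so 41 per arm and 82 in total.
- Applying 1.18 to that would give 82 × 1.18 ≈ 97, not 850. The Study Limitations description therefore does not match the calculation.

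**3. Does 720 already carry clustering?** The mean of 0.8^|i−j| over the 12 × 12 period pairs is 0.4913. The plan does not say how the CV enters, so two common treatments are used.
- (a) CV on the residual term only. Variance of a hospital mean: V = 1.64² × [0.4913ρ + (1 − ρ) × 1.25/(12m)].
- (b) CV on the whole design effect. Without CV, the design effect for 120 patients at ρ = 0.02 is 0.98 + 120 × 0.02 × 0.4913 = 2.16. The effective correlation is (2.159 − 1)/119 = 0.00974. With CV, the design effect is 1 + (1.25 × 120 − 1) × 0.00974 = 2.45, so V = 2.451 × 1.64²/120 = 0.0549.

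The standard error of the difference is √(2V/3), and power comes from the noncentral t with 4 df. For (b) at ρ = 0.02, SE = 0.191, noncentrality = 1.02/0.191 = 5.33 and power = 97.2%.

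| Patients per hospital-period | ICC 0.02, (b) to (a) | ICC 0.05, (b) to (a) |
|---|---|---|
| 10 (total 720) | 97.2% to 97.4% | 82.2% to 86.0% |
| 11.4 (total 822) | 97.8% to 98.1% | 83.1% to 87.1% |
| 14 (total about 1003) | 98.4% to 98.8% | 84.3% to 88.6% |

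With clustering fully included, 720 patients pass 80% even at the upper ICC. This agrees with the plan's own statement that 10 per period attains 80%, so 720 is already the clustered answer.

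**4. Dropout.**
- 1003 × 0.82 = 822, which is 28 below 850.
- 850/0.82 = 1036.6, so 1037 would be needed.
- From the clustered requirement: 720/0.82 = 878.05, so 879.
- At the observed 9% loss: 1003 × 0.91 = 913, above 850.

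**5. Does the inflation rescue a six-hospital design?** In the table, 40% more patients per hospital adds 1 to 1.5 percentage points at ICC 0.02 and 2 to 3 points at ICC 0.05.

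**The case against.** The strongest reply is that nothing is lost. The double counting pushes the target up, the 822 left after the worst-case loss exceeds 720, and power stays above 80% at both ICCs. This stands, and it limits the point to derivation and wording.

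Other parts of the reply also stand:
- The three faults do not combine to cause the shortfall against 850. It comes from the dropout step alone. The protocol also never calls the 850 evaluable patients; that is an inference from adding loss afterwards.
- The 18% is a declared worst case, twice the observed 9%. Participant Timeline has prehospital intervals obtained at admission, so 90-day loss bears mainly on the secondary outcomes, not on the outcome that was sized.
- A reader might go further and say that m should be 120, the patients per hospital, instead of 10. That does not follow. It would count clustering still more heavily (720 × 3.38 ≈ 2434), and the question disappears once the second inflation is removed.
- The small gain from more patients depends on the inputs. At an assumed SD of 2.5 h and ICC 0.02, treatment (a) moves from 75.2% to 81.1% for 10 to 14 per period; at ICC 0.05 it moves only from 53.3% to 56.6%. Whether the borrowed SD suits this setting is a separate issue.
- Study Limitations does admit that few clusters could affect power. What is too strong is the claim that the inflation overcomes this.

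The reply does not rescue the second use of 1.18, the dropout formula, the statement that inflation increases power, or the description of 720 as an individually randomised size.

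**Conclusion.** The point holds as an error in the stated derivation and rationale. Clustering enters twice (720 to 850). Dropout is multiplied instead of divided (1003 leaves 822, against 1037 needed to keep 850). The individually randomised size would be about 82, so Sample Size and Study Limitations describe the step incompatibly. These findings rest on the protocol's own inputs, with a two-sided test assumed for the 82.

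That the inflation does not overcome the few-cluster limitation rests on the table above. It assumes a two-sided test, 4 df, SD 1.64 h and a range for the CV treatment, because the calculator's figures are not shown.

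A reader might infer that the trial is too small. The documents do not support that: under the plan's own assumptions, 822 exceeds the 720 required.

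**What to change.** In Sample Size:
- Delete the second inflation formula and the claim that it increases power.
- State 720 as the requirement from the clustered calculation, 879 (720/0.82) if 18% loss is allowed for, and 1003 as a recruitment target with margin. Give 1037 only if 850 after loss is really intended.

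In Study Limitations:
- Remove the statement that an individually randomised size was inflated and that this overcomes the small number of clusters.
- Give the power of 3 hospitals per arm at ICC 0.02 and 0.05, with the df and CV treatment used.

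The cost is rewording two sections and reporting two power figures. No extra patients are needed.

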### Study Setting

This study will be conducted in 6 specialized teaching and regional referral hospitals in Uganda, including Kiryandongo, Jinja, Hoima, Fort Portal, Mubende, and Kampala International University Hospital. These facilities have similar characteristics and serve as teaching, residency, and internship sites for undergraduate and graduate medical doctors and nurses. The hospitals offer 24/7 emergency surgical services for trauma patients through multidisciplinary teams of orthopedic, general, and visiting neurosurgeons, as well as imaging, rehabilitation, and physiotherapy. Each surgical department in these facilities is typically composed of about 1-4 faculty members, 2-4 specialty residents often referred to as senior house officers, 4-6 interns, and 10-30 undergraduate medical trainees.

These facilities are suited for this study as they serve both rural populations and populations in newly created populous cities that are still struggling with urban planning. Uganda is the 8th most populous country in Africa and the 30th most populous country in the world [9], and its trauma surveillance systems are in the infancy stage with weak preaccident and postaccident responses [6,12]. Despite efforts made in the past decade by the Ugandan government to address the unmet need for trauma care through infrastructure development, such as equipping operating theaters and intensive care units (ICUs) in public hospitals, limited standardized preservice and in-service trauma training, prehospital delays, and human resource constraints still contribute to preventable trauma mortalities [14]. To guarantee the quality of data for this project, a prospective motorcycle trauma outcome registry (MOTOR) will be piloted at the participating 6 regional referral hospitals in parallel with this trial.

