#### Collection of Informed Consent

All participants or their legally authorized representatives (for minors and unconscious patients) will endorse a predesignated consent form document with their signatures in the presence of the principal investigator or research assistants (surgery specialty residents).

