### Interventions

#### Explanation for the Choice of Comparators

The intervention for this trial is based on the fourth edition of the RTTDC of the American College of Surgeons [20], which will be delivered to medical trainees, interns, and traffic law enforcement professionals at the 3 intervention study centers (intervention group). Specialty surgical residents will be trained as faculty who will later serve as trainers since they directly supervise interns and undergraduate medical students in Ugandan settings. The research and ethics committees approved training residents as opposed to specialists to avoid constraining the scarce specialized human resource as this is a trainee-capacity building trauma education program. Moreover, consultants rarely attend to trauma patients for immediate resuscitation as the first point of contact in Ugandan settings. The patient participants at intervention sites will be those with motorcycle accident–related injuries at any of the study sites. The comparator in this trial is a control group of hospitals that will offer standard care to eligible patients, without their care providers receiving the RTTDC training intervention.

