### Recruitment

The training will be advertised by hospital administrators, class representatives, and regional traffic law enforcement leaders, and course participants will be recruited by the principal investigator and the respective hospital administrators. The patient participants will be recruited by dedicated project officers at the accident and emergency departments.

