#### Interim Analyses

The Uganda National Council for Science and Technology accessed a preliminary report of the interim analysis, which was performed on August 28, 2022, when half of the sample size (n=500) was attained, and at its discretion, it recommended continuation of the study. The requisite characteristics for early termination set by the ethics committee included the occurrence of an index patient-reported adverse outcome definitely attributable to the study in accordance with the framework described by Okoniewska et al [48].

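### Patients are enrolled after hospitals are allocated, by people who know or can readily infer the arm, and allocation codes cannot hide an arm that is the hospital itself

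*Protocol article*

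**What the plan says.** **Timing.** Under Participant Timeline, hospitals are randomised three weeks before training starts. Patients are then enrolled concurrently at control and intervention sites through the MOTOR registry.

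**Who enrols.** Under Recruitment, "The patient participants will be recruited by dedicated project officers at the accident and emergency departments". Implementation adds that these project medical officers also serve as outcome assessors.

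**Who takes consent.** Under Collection of Informed Consent, forms are signed "in the presence of the principal investigator or research assistants (surgery specialty residents").

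**What else those people do.** Under Explanation for the Choice of Comparators, "Specialty surgical residents will be trained as faculty who will later serve as trainers". Intervention Description makes trained residents team leaders and round-the-clock advisers. The section on the coordinating center has the principal investigator supporting the intervention teams in weekly audit meetings.

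**Blinding.** Concealment Mechanism, Who Will Be Blinded, and Plans for Assessment and Collection of Outcomes all describe the outcome assessors as blinded. The stated means is allocation codes.

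**Numbers.** The Sample Size section gives "there will be 502 participants per arm and about 168 individuals per cluster". For feasibility it cites one regional referral hospital where "a total of 900 motorcycle accident–related injuries were recorded during a 3-year period", of which 278 were musculoskeletal and 142 neurological.

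**Registry and log.** Study Setting says that "a prospective motorcycle trauma outcome registry (MOTOR) will be piloted at the participating 6 regional referral hospitals". The patient exclusion criteria require a count of ineligible patients, with reasons, in both arms. They do not mention eligible patients who were not enrolled.

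**The concern.** In a cluster trial, randomisation balances hospitals. It protects the patient comparison only if who enters does not depend on the arm. When patients are identified and consented after allocation by people aware of the arm, quicker arrivals or milder injuries can enter more readily on one side, even without intent. A first primary outcome measured from accident to admission, and 90-day mortality, would both respond directly. A mixed model with three hospitals per arm can adjust for measured covariates, but it cannot otherwise separate such a shift from an effect of training.

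The risk matters more when many more patients present than are needed, because an uneven intake then need not show up as a recruitment shortfall. It also weakens the blinding claim, since the same officers enrol patients and assess outcomes.

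**Working it through.** **1. The plan's target.** Inputs are all from Sample Size: 10 patients per cluster-period, 12 periods, 3 hospitals per arm, ICC 0.02, 18% loss.

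- Per arm: "10 participants per cluster period multiplied by 12 cluster periods multiplied by 3 clusters, yielding a total of 360 participants". Two arms: 720.
- Design effect: 720 × (1 + 9 × 0.02) = 849.6, stated as 850.
- Loss: 850 × 1.18 = 1003, as stated.
- 1003 / 2 = 501.5, stated as 502. 502 / 3 = 167.3, stated as about 168.

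The target reproduces. (Inflating by division, 850 / 0.82 = 1037 or about 173 per hospital, is a separate matter. The first ratio below would become 900 / 173 = 5.2.)

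**2. Patient volume against target, per hospital over 36 months.**

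- All recorded motorcycle injuries: 900 / 36 = 25 per month, against 168 / 36 = 4.7 needed. Ratio 900 / 168 = 5.4.
- Musculoskeletal plus neurological: 278 + 142 = 420, or 11.7 per month. Ratio 420 / 168 = 2.5. This assumes that the two groups do not overlap; overlap would lower it.
- If 50% to 90% of the 900 were eligible (an assumed range, not in the documents): 450 / 168 = 2.7 to 810 / 168 = 4.8.

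At such volumes, taking every patient would fill a hospital's target in 168 / 25 = 6.7 months to 168 / 11.7 = 14.4 months, against 36 planned.

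**3. The observed pace.** Interim Analyses dates the interim look to 28 August 2022, "when half of the sample size (n=500) was attained". Recruitment began on 1 September 2019 and was suspended from March 2020 to March 2021. That leaves about 22.9 to 24.9 active months, depending on where in March the suspension began and ended.

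- 500 / (6 × 22.9) = 3.6 and 500 / (6 × 24.9) = 3.3 patients per hospital per month.
- Times 3 months: about 10.0 to 10.9 per cluster-period, close to the planned 10.

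This is below the 11.7 to 25 per month at the cited hospital. It fits partial enrolment at sites of that size, but equally full enrolment at sites with fewer eligible patients, so it does not settle the question.

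**4. Roles set against blinding.**

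- *Principal investigator:* witnesses consent, recruits course participants, supports the intervention teams weekly. Knows the arm.
- *Surgery residents at intervention hospitals:* witness consent, teach the course, lead the teams. Know the arm by their role.
- *Project medical officers:* enrol patients and assess outcomes on site, and are stated to be blinded. The course runs for two days in the hospital's own rooms, is repeated for successive cohorts, and aims at 80% or more of each. Codes can conceal the sequence before assignment. They cannot afterwards conceal whether one's own hospital is being trained. That the officers know the arm is an inference, though a strong one.

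**The case against.** The strongest reply is that the protocol nowhere says staff choose patients. It names project medical officers as enrollers and calls them blinded, and witnessing a signature is not selecting a patient. A condensed article may leave an enrolment rule to the full protocol or to the registry appendix. Ineligible patients are logged by arm and baseline characteristics are compared. This stands as far as it goes: silence on consecutive enrolment is not itself a fault, and deliberate selection is not documented.

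Three stronger readings are tempting, and the documents support none of them.

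- *Eligibility admits five times the patients needed.* The 900 are recorded injuries at one hospital, before the 24-hour window, the exclusions and consent. The 5.4 is an upper figure.
- *The interim pace shows that most patients were passed over.* That divides the trial's pace by the same single hospital's volume, so it adds no independent evidence.
- *The bias can be put in minutes.* If, in one arm only, each SD of later arrival (1.64 h, from the cited US study) made enrolment 20% less likely, normally distributed times would shift by −ln(0.8) × 1.64 = 0.37 h, or 22 minutes. The 20% has no source in the documents, so this illustrates a mechanism and is not an estimate.

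The reply does not remove the conflict in the text. For the principal investigator and for residents at intervention sites, knowledge of the arm follows from their stated roles. The stated means of blinding the officers cannot do what is claimed. The log of ineligible patients would not reveal eligible patients left out.

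**Conclusion.** The point holds in this form: identification and consent follow allocation, people at or near enrolment know or can readily infer the arm, and the blinding statements are not compatible with the roles described. Differential enrolment between arms is therefore possible, and the protocol states no check that would detect it.

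The room for it is roughly 2.5 to 5.4 eligible patients per patient needed, on the assumption that the other five hospitals resemble the cited one and that most recorded cases in the chosen base would qualify. At sites with lower volume the room could be much smaller. Neither the direction nor the size of any bias can be derived from the documents, and nothing in them shows that selection took place.

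**What to change.** 1. Reconcile Collection of Informed Consent, Explanation for the Choice of Comparators, Intervention Description and the coordinating-center section with Concealment Mechanism, Implementation and Who Will Be Blinded. Enrolment and consent should rest with the project medical officers, not with course faculty or the principal investigator. With recruitment over, state who actually took consent at each hospital, and apply the rule to any further enrolment.
2. Withdraw the claim that enrolling staff and outcome assessors are blinded to arm, or limit it to what was achieved.
3. Report numbers screened, eligible and enrolled by hospital and three-month period, and state how eligible patients were taken in.
4. Before the analysis planned for Spring 2024, prespecify two checks, to be run where MOTOR or hospital records and approvals allow: a comparison by arm of enrolled with eligible-but-not-enrolled patients (age, GCS, KTS, mode of arrival), and a sensitivity analysis of accident-to-admission time in all eligible patients or with enrolment-probability weights.

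Items 1 and 2 cost a few sentences, and item 3 a table if screening counts were kept. Item 4 may not be feasible. The documents do not show that MOTOR holds patients who were not enrolled, such records may be incomplete or absent, and using data from patients who did not consent would need approval. If no such records exist, the report should say so and list selection after allocation as a limitation.
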